## Abstract

**Background:**

Atopic dermatitis (AD) is a prevalent chronic and recurrent inflammatory skin disease. Guidelines for the treatment and care of AD suggest that appropriate bathing can facilitate the repair of skin lesions. MuShengshu is a weakly acidic bath solution that contains traditional Chinese medicine ingredients. Previous studies indicate its potential to alleviate pruritus and promote the healing of skin lesions in patients with dermatosis. However, high-quality evidence is still limited.

**Objectives:**

This randomized, double-blind, placebo-controlled clinical trial aims to assess the efficacy and safety of MuShengshu (MSS) combined with foundational therapies in patients with mild-to-moderate AD.

**Methods:**

A total of 66 patients with mild-to-moderate AD will be enrolled at the Shanghai Skin Disease Hospital from August 2025 to June 2026. Patients will be randomly assigned in a 2:1 ratio to either the treatment group (MSS combined with foundational therapies, *n* = 44) or the control group (MSS placebo combined with foundational therapies, *n* = 22). Patients will receive MSS or MSS placebo once daily, for 4 months. Meanwhile, the foundational therapies include desonide cream for mild AD and triamcinolone acetonide cream for moderate AD, both of which will be applied twice daily for 2 weeks. Additionally, all patients will receive urea ointment twice daily for 4 weeks. The primary outcome indicator is EASI_50_, defined as the proportion of patients achieving ≥50% improvement in the Eczema Area and Severity Index (EASI) score at week 4 from baseline. The secondary outcome indicators include the EASI, Visual Analogue Scale (VAS), Investigator’s Global Assessment (IGA), and Dermatology Life Quality Index (DLQI), which will be assessed at baseline (week 0), weeks 1, 2, 4, and 16. In this study, statistical analyses will be conducted using SAS 9.4 software, with statistical significance being defined as a two-tailed *α* level of 0.05.

**Results:**

In this study, ethical approval was granted in March 2025, with registration completed in the International Traditional Medicine Clinical Trial Registry in June 2025. Recruitment of participants began in August 2025 and is anticipated to completed by June 2026. Data analysis is set to start in August 2026, with preliminary trial results expected to be submitted for peer-reviewed publication by December 2026.

**Conclusion:**

Findings in this study are expected to provide evidence for the incorporation of traditional Chinese herbal bath solutions into the comprehensive management of AD.

**Clinical trial registration:**

https://www.chictr.org.cn/, Identifier ITMCTR2025001206.

## Introduction

Atopic dermatitis (AD) is a prevalent chronic and recurrent inflammatory skin disease characterized by intense itching, recurrent attacks, dry skin, and typical eczematous lesions (1). The pathogenesis of AD is complex, involving a multifactorial interplay of genetic, immunological, and environmental factors (2). Beyond its cutaneous manifestations, AD profoundly impacts patients’ quality of life, contributing to sleep disturbances, cognitive impairments, and an increased risk of anxiety and depression (3). The incidence of AD has been rising globally, particularly among the pediatric population (4). AD is associated with a considerable disease burden, representing the highest impact among all non-fatal skin conditions (5).

In recent years, numerous treatment options for AD have been developed, including emollients, corticosteroids, calcineurin inhibitors, antihistamines, and biologics (6–8). However, current therapeutic options still have limitations, such as side effects associated with long-term use of potent corticosteroids, insufficient efficacy or frequent recurrences in some patients, and concerns about the safety and applicability of systemic therapies (9–11). Therefore, the development of new safe, effective, and easily manageable treatment options remains an important clinical challenge with substantial societal implications.

The guidelines for AD treatment and care suggest that appropriate bathing facilitates the repair of skin lesions (12, 13). Previous studies indicate that the development of AD is closely associated with impaired skin barrier function, which compromises the skin’s ability to retain moisture and defend against external irritants (14). The pH value of skin surface in healthy individuals typically ranges from 4.5 to 6.5, establishing a weakly acidic environment crucial for maintaining the integrity of the skin barrier and defending against pathogenic microorganisms (15). However, currently many commercial cleaning and skincare products are alkaline. The alkalinity can disrupt the skin’s acid–base balance, potentially increase the risk of developing or exacerbating chronic skin conditions (16). So prolonged use of such products may adversely affect individuals with dermatological issues. In contrast, traditional Chinese herbal bath solutions offer multifaceted therapeutic benefits. Formulated to restore the skin barrier and address specific dermatological disorders, these solutions also provide essential cleansing and nourishment. This synergistic approach not only aims to shorten treatment duration but also helps reduce the likelihood of recurrence (17).

MuShengshu (MSS) is a weakly acidic bath solution that contains traditional Chinese medicine ingredients. This herbal bath solution is exclusively developed, extracted, and produced by Guizhou Langyoutang Pharmaceutical Co., Ltd. Its core botanical ingredients include Cortex Dictamni, Radix Sophorae Flavescentis, Fructus Kochiae, Rhizoma Smilacis Glabrae, Isatis Root, Golden Cypress, and Agastache Rugosa. Studies indicate that MSS solution aligns with the natural pH of human skin, thereby effectively preserve the integrity of the skin barrier (18). Previous studies indicate its potential to alleviate pruritus and promote the healing of skin lesions in patients with dermatosis (19). However, there is a lack of high-quality evidence-based medical data to support these findings. We implement this randomized, double-blind, placebo-controlled clinical trial to evaluate the efficacy and safety of MSS in patients with AD. We hypothesize that MSS combined with foundational therapies will contribute to symptom relief in patients with mild-to-moderate AD. To our knowledge, this is the first trial to evaluate the efficacy and safety of a traditional Chinese herbal bath solution as an adjunct to standard therapy in mild-to-moderate AD. The results are expected to provide robust evidence for its incorporation as an adjunctive treatment in clinical practice, thereby facilitating long-term management and reducing the disease burden of AD.

## Methods

### Study design

This randomized, double-blind, placebo-controlled trial is designed to evaluate the efficacy of MSS combined with foundational therapies in improving skin lesions and relieving pruritus in patients with mild-to-moderate atopic dermatitis (AD). The study protocol adheres to the SPIRIT (Standard Protocol Items: Recommendations for Interventional Trials) guidelines (20). A total of 66 patients with mild-to-moderate AD will be enrolled at the Shanghai Skin Disease Hospital during August 2025 and June 2026. Patients will be randomly assigned in a 2:1 ratio to either the treatment group (MSS combined with foundational therapies, *n* = 44) or control group (MSS placebo combined with foundational therapies, *n* = 22). The study flowchart is shown in Figure 1.

**Figure 1 fig1:**
[figure not shown]
Clinical trial flowchart.

### Inclusion criteria

The inclusion criteria for patients with mild-to-moderate AD are as follows: (1) a diagnosis of mild-to-moderate AD based on the Williams criteria (Guideline for Primary Care of Atopic Dermatitis, 2022 edition (21)); (2) male or female patients aged 18–50 years; (3) the target skin lesion has a diameter of 2–10 cm and is mainly located on the limbs or trunk; (4) the skin lesions cover less than 10% of the body surface area (BSA); and (5) patient voluntarily signs the informed consent form and agrees to participate in the study, with commitment to regular follow-up as required.

### Exclusion criteria

The exclusion criteria are as follows: (1) patients who are pregnant, breastfeeding, or planning to become pregnant; (2) patients who have received local treatment or phototherapy within the past 2 weeks, or have received systemic treatment for AD within the past 3 months; (3) patients with serious systemic conditions, including heart, lung, liver, kidney, gastrointestinal or mental illnesses; (4) patients with systemic or active skin diseases that could interfere with the evaluation; (5) patients with scars, tattoos, birthmarks, or sunspots that may affect the assessment of skin lesions; (6) patients who have participated in other clinical trials within the past month; and (7) patients with communication barriers that prevent them from independently completing the case report form (CRF).

### Sample size

The sample size was calculated based on the EASI_50_ achievement rate at week 4, which was defined as the proportion of patients who achieved ≥50% improvement in Eczema Area and Severity Index (EASI) score from baseline to week 4. According to preliminary observation data, we assume that the EASI_50_ achievement rate at week 4 would be 85% in the treatment group and 50% in the control group. Based on a 2:1 randomization ratio, the sample size is calculated with PASS 15.0 software. Setting a two-tailed *α* level at 0.05 and statistical power at 80%, the calculation yields a requirement of 40 patients for the treatment group and 20 for the control group. Considering a 10% dropout rate, the final enrollment target is set at 44 patients for the treatment group and 22 patients for the control group. The specific formula for calculating sample size was as follows:
$$n_{2}=\frac{\frac{p_{1}\times (1-p_{1})}{k}+p_{2}\times (1-p_{2})}{{\left(p_{1}-p_{2}\right)}^{2}}\times {\left(\mu_{\alpha /2}+\mu_{\beta }\right)}^{2},n_{1}=k\times n_{2}$$

### Randomization

In this study, stratified randomization will be employed, with stratification factors including patient gender (male, female) and disease severity (mild, moderate). A total of 66 patients with mild-to-moderate atopic dermatitis (AD) will be randomly assigned to either the treatment group or the control group in a 2:1 ratio, based on these stratification factors. Randomization will be performed by an independent statistician using the clinical research support system to generate 66 random numbers. Allocation concealment will be ensured through the use of sequentially numbered, opaque envelopes, which will be securely stored with restricted access at the clinical research center of Shanghai Skin Disease Hospital.

### Blinding

In this study, both of patients with mild-to-moderate AD and dermatologists will be blinded to the treatment allocation. Additionally, outcome assessors, data collectors, and statisticians responsible for data analysis will also remain unaware of the group assignments throughout the trial period to prevent potential information bias.

### Interventions

Patients in the treatment group will take a daily bath using MSS for a period of 4 months. To ensure the proper application of MSS, dermatologists will advise patients to first moisten their entire body with warm water, then apply 8 g of the product (4 g per press) to the skin surface. Massage gently for 3 to 5 min to ensure full absorption, and followed by rinsing with warm water. Patients in the control group will also take a daily bath using MSS placebo for a period of 4 months. The MSS placebo was formulated to be devoid of any Chinese herbal constituents, containing only the base excipients. It was manufactured by the same entity to guarantee perfect consistency with the active treatment in all physical attributes—appearance, weight, color, odor, and packaging. The guidance and application of MSS placebo in the control group will be identical to that for the treatment group.

In this study, both of patients in the treatment group and control group will receive the same foundational therapeutic regimen. The foundational therapies include desonide cream for mild AD and triamcinolone acetonide cream for moderate AD, both of which will be applied twice daily for 2 weeks. Additionally, all patients will receive urea ointment twice daily for 4 weeks. In this study, no additional treatment is permitted, and emergency interventions require documentation in detail and will result in the withdrawal of participation.

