#### Secondary outcomes

The secondary outcome indicators include the EASI, Visual Analogue Scale (VAS), Investigator’s Global Assessment (IGA), and Dermatology Life Quality Index (DLQI) (23, 24). These indicators will be assessed at baseline (week 0) and subsequently at weeks 1, 2, 4, and 16. A detailed study schedule is presented in Table 1, which specifies the evaluation time points for each measure.

**Table 1 tab1:** Study schedule of the MuShengshu clinical trial (16 weeks).

Indicator	Baseline	Follow-up			
	Visit 1 (week 0)	Visit 2 (week 1)	Visit 3 (week 2)	Visit 4 (week 4)	Visit 5 (week 16)
Informed consent	✓	–^a^	–	–	–
Demographic features	✓	–	–	–	–
Family medical history	✓	–	–	–	–
Physical examination	✓	–	–	–	–
Inclusion/exclusion criteria check	✓	–	–	–	–
Randomization	✓	–	–	–	–
EASI^b^	✓	✓	✓	✓	✓
VAS^c^	✓	✓	✓	✓	✓
IGA^d^	✓	✓	✓	✓	✓
DLQI^e^	✓	✓	✓	✓	✓
Concomitant medications	–	✓	✓	✓	✓
Adverse events	–	✓	✓	✓	✓

a Not applicable.

b EASI: Eczema Area and Severity Index.

c VAS: Visual Analogue Scale.

d IGA: Investigator’s Global Assessment.

e DLQI: Dermatology Life Quality Index.

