### VAS

Pruritus severity in patients with mild-to-moderate AD will be assessed using the validated VAS (25). This method typically employs a 10-centimeter linear scale, with one end labeled “0 points” for “no pruritus” and the other end labeled “10 points” for “severe pruritus.” Patients mark the scale according to their pruritus perception, and evaluators determine the score by measuring the distance from the marked point to the “no pruritus” end. During each visit, participants will evaluate their peak pruritus severity over the preceding 24 h using the VAS.

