### Data collection and management

Trained dermatologists will gather data utilizing a standardized CRF, which consists of five sections: (1) demographic information, including age, gender, and census registration; (2) family medical history related to AD; (3) physical examination data such as height, weight, and body mass index (BMI); (4) baseline (week 0) and follow-up scores for EASI, VAS, IGA, and DLQI at weeks 1, 2, 4, and 16; and (5) information on concomitant medications and any adverse events.

The database will be developed using Epidata 3.1 software, featuring comprehensive validation rules. Data for all 66 participants will be input using a double data entry method conducted by two independent operators. Consistency checks between the two datasets will help identify discrepancies, which will then be resolved by cross-referencing with the original CRF until complete concordance is achieved through iterative verification.

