### Statistical analysis

In this study, data analysis will be conducted using the SAS 9.4 statistical software. Normally distributed quantitative variables will be summarized as mean and standard deviation (SD), while skewed distributions will be represented by the median and interquartile range (IQR). For inter-group comparisons of quantitative variables with normal distribution, the Student *t*-test will be utilized, whereas the Wilcoxon rank-sum test will be applied for skewed quantitative data. Repeated measurement data will be analyzed using repeated measures analysis of variance. Categorical variables will be presented as frequencies and proportions (%), with differences between groups evaluated through chi-square tests or Fisher’s exact tests.

Data analysis in this study will follow the intention-to-treat (ITT) principle, including all randomized participants regardless of adherence to the protocol or completion of the study (28). Missing data will be addressed under the missing-at-random assumption using sequential regression multiple imputation, which estimates missing values based on regression models that consider the relationships among all other variables (29). Furthermore, analyses will be performed on both the full analysis set (FAS) and the per-protocol set (PPS), with a *p*-value of less than 0.05 (two-tailed) is viewed as statistically significant.

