For the treatment and long-term management of AD, skin barrier repair and maintenance are essential. Guidelines for AD treatment suggest that appropriate bathing can facilitate the repair of skin lesions (12, 13). Previous studies indicate that various bath solutions can efficiently restore skin barrier function and increase skin hydration (40, 41). A meta-analysis has demonstrated that traditional Chinese herbal bath solutions can effectively alleviate clinical pruritus (42). MSS, as a weakly acidic solution containing over seven core Chinese herbal components, helps inhibit inflammation and preserve skin barrier integrity (43). Numerous studies have demonstrated that the core Chinese herbal components can exert anti-inflammatory effects through three key pathways: inhibiting the release of inflammatory mediators, regulating immune cell activity, and reducing oxidative stress (44–46). By inhibit inflammation, repairing the barrier, alleviating symptoms, and expediting recovery, this herbal bath solution anticipated to substantially improve clinical outcomes in AD patients. Additionally, this study design includes foundational therapies (desonide cream for mild AD and triamcinolone acetonide cream for moderate AD) alongside rescue medication (levocetirizine tablets for severe pruritus, 1 tablet each day), ensuring that all AD patients receive standardized background care throughout the trial.

Results in this study are expected to provide new insights and approaches for the prevention and treatment of AD. To our knowledge, this study is the first clinical trial to assess the clinical efficacy and safety of a traditional Chinese medicine solution combined with foundational therapies in the treatment of mild-to moderate AD. The evaluation will be conducted through a multidimensional approach, encompassing assessments of skin lesion severity, intensity of pruritus, and overall quality of life. The results of this study will provide robust evidence for the incorporation of traditional Chinese herbal bath solutions into clinical practice as a supplementary treatment modality for AD, thereby effectively facilitate long-term management of AD. We are planned to disseminate our findings through publication in internationally peer-reviewed journals.

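### The Methods forbid additional treatment and withdraw patients after emergency treatment, but the Discussion provides daily levocetirizine rescue; nothing says which rule applies

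*Protocol article*

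**What the plan says.** **Protocol article, Interventions.** The section lists the foundational regimen: desonide (mild disease) or triamcinolone acetonide (moderate disease) for 2 weeks, and urea ointment for 4 weeks. It then states that "no additional treatment is permitted, and emergency interventions require documentation in detail and will result in the withdrawal of participation". Levocetirizine is not named there, nor anywhere else in the Methods or the abstract.

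**Protocol article, Discussion.** The design is said to include the topical corticosteroids "alongside rescue medication (levocetirizine tablets for severe pruritus, 1 tablet each day), ensuring that all AD patients receive standardized background care throughout the trial".

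**Related provisions:**
- Secondary outcomes (EASI, VAS, IGA, DLQI): "These indicators will be assessed at baseline (week 0) and subsequently at weeks 1, 2, 4, and 16".
- VAS: "participants will evaluate their peak pruritus severity over the preceding 24 h using the VAS".
- Data collection and management: the case report form (CRF) takes "information on concomitant medications and any adverse events". Which medications are allowed is not stated.
- Withdraw and dropout: only withdrawal chosen by the patient is covered.
- Statistical analysis: intention-to-treat, "including all randomized participants regardless of adherence to the protocol or completion of the study". Also: "Missing data will be addressed under the missing-at-random assumption using sequential regression multiple imputation".

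**The concern.** Itch is a leading symptom of atopic dermatitis, and relieving it is a stated aim of the trial (Study design). Severe itch during follow-up is therefore an event the protocol has to handle clearly. As written, an investigator who follows Interventions gives nothing further, and withdraws the patient if emergency treatment is needed. An investigator who follows the Discussion prescribes levocetirizine and keeps the patient in.

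Three things depend on the answer:
- **Which data exist.** If rescue is allowed, the 24-hour peak pruritus VAS and the DLQI may be scored while the patient takes an antihistamine. If the patient is withdrawn, the later scores are imputed.
- **Who is compliant.** Whether a levocetirizine user has broken the protocol bears on the per-protocol set (Statistical analysis) and on the reporting of violations to the ethics committee (Ethical considerations).
- **Whether patients are handled alike.** Recruitment began in August 2025 (Results), so an unsettled rule may already be applied differently from one patient to the next.

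**Working it through.** **Step 1: set the two rules side by side.**

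| Question | Interventions | Discussion |
|---|---|---|
| Treatment beyond the topical regimen? | None permitted | Levocetirizine for severe itch, 1 tablet daily |
| What follows if more is needed? | An emergency intervention is documented and the patient is withdrawn | Rescue is presented as part of background care for the whole trial |
| Exception or cross-reference? | None | None |

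If levocetirizine is additional treatment, Interventions bars it. If it is an emergency intervention, every user is withdrawn, which does not fit care described as running throughout the trial. If it is an unstated exception, the operative section should say so. The sections on schedule, withdrawal, data collection, analysis and ethics do not settle the matter.

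**Step 2: find where missing data would hurt.** Missing at random lets exit depend on recorded scores. It fails only to the extent that exit depends on worsening that was never recorded. The corticosteroid ends at week 2 and urea at week 4. Visits fall at weeks 0, 1, 2, 4 and 16. The unobserved interval after foundational therapy is 16 − 4 = 12 weeks, and 12/16 = 75% of follow-up. The exposure is therefore greatest for week-16 outcomes. The primary outcome, EASI50 at week 4, is touched only by withdrawal before week 4.

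**Step 3: illustrate for the primary outcome.** The document gives no rescue or withdrawal rate, so it has no figure of its own to reproduce on this point. The inputs are the assumed week-4 EASI50 rates (85% and 50%) and the arm sizes (44 and 22), all from Sample size.

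- Expected MSS responders: 0.85 × 44 = 37.4, leaving 6.6 non-responders.
- Expected control responders: 0.50 × 22 = 11, leaving 11 non-responders.
- Planned difference: 85.0 − 50.0 = 35.0 points.

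Assume that w_t MSS and w_c control non-responders are withdrawn before week 4 and imputed at the completers' rate in their arm. The rates become 37.4/(44 − w_t) and 11/(22 − w_c).

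| Assumed withdrawals | MSS | Control | Difference (points) |
|---|---|---|---|
| (a) w_t = 0, w_c = 1 | 37.4/44 = 85.0% | 11/21 = 52.4% | 32.6 |
| (a) w_t = 0, w_c = 2 | 85.0% | 11/20 = 55.0% | 30.0 |
| (a) w_t = 0, w_c = 3 | 85.0% | 11/19 = 57.9% | 27.1 |
| (b) 1/11 (9%) of non-responders in each arm: 0.6 and 1 | 37.4/43.4 = 86.2% | 52.4% | 33.8 |
| (b) 2/11 (18%): 1.2 and 2 | 37.4/42.8 = 87.4% | 55.0% | 32.4 |
| (b) 3/11 (27%): 1.8 and 3 | 37.4/42.2 = 88.6% | 57.9% | 30.7 |

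Differences are taken from unrounded rates. The direction is not fixed: with w_t = 1 and w_c = 0, the difference is 37.4/43 − 11/22 = 87.0 − 50.0 = 37.0 points, above the planned 35.0.

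**The case against.** **A consistent reading can be built.** If rescue belongs to the design, the ban covers only what lies outside the design, and emergency interventions form a separate class that leads to withdrawal. Recording concomitant medication at every follow-up visit fits some permitted use. This is also a journal article, and fuller rescue rules may sit in the complete protocol. The reading is possible, but it has to be inferred against an absolute statement in the operative section, and recording a drug does not show that it is allowed. The problem is also not an omission that condensation explains: the article states two rules that disagree.

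**The illustration is an extreme.** Imputing at the completers' rate amounts to a complete-case analysis within each arm. The plan's sequential regression would use any scores recorded at weeks 1 and 2. The illustration also assumes that every withdrawn patient is a non-responder, and scenario (a) sets MSS withdrawals at zero without support from the document. It addresses week-4 EASI50, the less exposed and better observed outcome. All of this stands. The figures show an unfavourable case, not the expected behaviour of the plan, and the finding does not depend on them.

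**Keeping emergency-treated patients in follow-up is a separate point.** This is partly right: that advice would still apply if the two sections agreed. It belongs here because withdrawal is the consequence that Interventions attaches to further treatment, and it sits poorly with the intention-to-treat aim.

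**Recruitment has begun.** A change now could leave two ways of handling patients within one trial. This stands as a cost.

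**Conclusion.** The concern holds. The document bars all additional treatment in one place and provides daily levocetirizine rescue in another, and it never says which governs. Followed literally, Interventions ends follow-up for patients who need emergency treatment and leaves their later scores to imputation.

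The effect is mainly on secondary outcomes (pruritus VAS, DLQI and the week-16 assessments) and cannot be quantified without a rescue or withdrawal rate. For the primary outcome, under the stated extreme assumptions, the planned 35.0-point difference falls to between 32.6 and 27.1 points if 1 to 3 control non-responders alone leave. It falls to between 33.8 and 30.7 points if equal shares of non-responders leave both arms. It could rise if a clearly larger share of MSS non-responders left. The point should be fixed; it does not undermine the trial as a whole.

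**What to change.** Amend Interventions to state one rule. The preferred form:
- Levocetirizine, 1 tablet daily, is the only rescue permitted for severe pruritus.
- Its dose and dates are entered in the existing concomitant-medication section of the CRF.
- Patients who use it, or who need emergency treatment, stop study treatment if necessary but stay in follow-up and are assessed at every visit to week 16.

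If no rescue is intended, delete it from the Discussion and still keep emergency-treated patients in follow-up. Because recruitment has started, the amendment should also say which rule has been applied so far and from what date the stated rule holds.

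**Cost:** one protocol amendment, reported to the ethics committee, and a memo to the single site. Concomitant medication is already recorded at weeks 1, 2, 4 and 16, so no new visit is needed. The drawbacks are that some scores will be observed after rescue use and that patients treated before the change may have been handled differently.

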### Adverse events

In this study, patients with mild to moderate AD will be made aware of any potential risks associated with the study prior to signing the informed consent form. Adverse events are defined as any unintended signs, symptoms, or diseases that occur following treatment and are not necessarily linked to the intervention. All adverse events will be documented accurately in the CRF. Additionally, dermatologists will provide appropriate treatment for any adverse events encountered, and both the adherence of AD patients and the occurrence of adverse events will be recorded.

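### Withdrawing a patient from participation after an emergency intervention turns outcomes that could be observed into imputed ones, and the unqualified ban on additional treatment conflicts with the levocetirizine rescue in the Discussion

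*Protocol article*

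**What the plan says.** Interventions gives both arms the same foundational regimen: desonide (mild AD) or triamcinolone acetonide (moderate AD) for 2 weeks, and urea ointment for 4 weeks. It then says that "no additional treatment is permitted, and emergency interventions require documentation in detail and will result in the withdrawal of participation". The term for emergency interventions is not defined.

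The Discussion says the design includes the foundational therapies "alongside rescue medication (levocetirizine tablets for severe pruritus, 1 tablet each day", so that all patients have standardised background care. Levocetirizine is not named in Interventions.

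Statistical analysis applies intention to treat, "including all randomized participants regardless of adherence to the protocol or completion of the study". For missing values it says: "Missing data will be addressed under the missing-at-random assumption using sequential regression multiple imputation". Analyses are also planned on a full analysis set and a per-protocol set.

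Table 1 schedules EASI, VAS, IGA and DLQI at weeks 0, 1, 2, 4 and 16, and records concomitant medications and adverse events at every follow-up visit. The primary outcome is EASI50 at week 4.

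**The concern.** Two things are at stake.

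First, the rule merges stopping the bath product with leaving the study. Nothing in the article keeps a patient on the visit schedule after an emergency intervention. If the intervention was for worsening AD before week 4, that patient has probably not responded. The plan would nevertheless replace the outcome by imputed values, which can credit the patient with a partial chance of EASI50. The data are lost through a rule of the protocol, not because the patient refused or could not be reached.

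Second, Interventions and the Discussion give dermatologists different instructions about levocetirizine. A patient who takes it could be following the protocol, be in breach of it (which bears on the per-protocol set), or be thought due for withdrawal. Pruritus VAS is a secondary outcome that an antipruritic rescue is meant to change, so the status of such patients matters for its interpretation.

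**Working it through.** **A. What the withdrawal rule does to the data.** The plan states no rate of emergency intervention, so it has no figure of its own to reproduce here. The timing follows from the schedule:

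- Event before the week-4 visit: week-4 and week-16 outcomes are lost.
- Event after the week-4 visit: only week-16 outcomes are lost; the primary outcome is already observed.
- Event between weeks 2 and 4: topical steroid has just stopped and there is no visit in the interval. The last observed scores (weeks 1 and 2) were taken during the steroid course and may look favourable. Imputation from them need not reflect the flare.
- Event between weeks 4 and 16: no visit for 12 weeks, and imputation rests on scores from week 4 or earlier.

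**B. Size per patient withdrawn before week 4.** Inputs: arms of 44 and 22; planning rates from Sample size, where the EASI50 "achievement rate at week 4 would be 85% in the treatment group and 50% in the control group". The planned difference is 85 − 50 = 35 points.

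Share of the arm's primary outcomes moved from observed to imputed:
- MSS: 1/44 = 2.3%
- Control: 1/22 = 4.5%

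Overstatement of the arm's rate, assuming a true non-responder imputed at the planning rate:
- MSS: 0.85 × 1/44 = 0.0193, or 1.9 points
- Control: 0.50 × 1/22 = 0.0227, or 2.3 points

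If poor earlier scores lower the imputed probability, these figures fall, down to 0.

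Effect on the difference (MSS minus control), same assumption:
- One patient in each arm: 1.93 − 2.27 = −0.3 points
- Two in MSS and one in control (4.5% of each arm): 3.86 − 2.27 = +1.6 points

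The sign therefore depends on how withdrawals split between the arms.

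**C. Illustration at arm level.** Assumptions: 85% and 50% are the rates with withdrawn patients counted as non-responders; all withdrawn patients are non-responders; imputation returns the rate among completers in the same arm, that is rate/(1 − withdrawn share). The withdrawal shares are assumed and do not come from the article.

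| Withdrawn before week 4, MSS / control | MSS | Control | Difference | Shift from 35 points |
|---|---|---|---|---|
| 0% / 10% | 85.0% | 0.50/0.90 = 55.6% | 29.4 | −5.6 |
| 5% / 10% | 0.85/0.95 = 89.5% | 55.6% | 33.9 | −1.1 |
| 10% / 10% | 0.85/0.90 = 94.4% | 55.6% | 38.9 | +3.9 |
| 5% / 20% | 89.5% | 0.50/0.80 = 62.5% | 27.0 | −8.0 |
| 0% / 20% | 85.0% | 62.5% | 22.5 | −12.5 |

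The 20% rows go beyond the 10% dropout planned in Sample size and mark an extreme.

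**D. The levocetirizine conflict.** Interventions lists the foundational therapies (steroid cream and urea) and then bans anything additional, without exception. The Discussion says the design also includes an antihistamine rescue. One could try reading the ban as covering only other AD treatments, but the Introduction lists AD treatment options as "emollients, corticosteroids, calcineurin inhibitors, antihistamines, and biologics", so an antihistamine falls inside that reading too. As written, the two statements cannot both be followed.

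**The case against.** The strongest reply is that the term for emergency interventions is undefined and could cover an allergic reaction or an unrelated event, and that the article does not say outright that visits stop. Follow-up after withdrawal is detail that a fuller protocol may hold, and sensitivity analyses usually belong in an analysis plan. The imputation uses all other variables, so anyone leaving after week 2 contributes three sets of scores. Patients have lesions on less than 10% of body surface and receive steroid for two weeks, so emergency AD treatment before week 4 may be rare. Finally, the ban could mean treatment beyond a regimen that already includes levocetirizine.

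Much of this stands. Not every event need relate to prognosis, early events may be few or none, and the absence of a sensitivity analysis from the article is not itself an error. What does not fall is the stated rule: the article says participation ends, and the only handling it states for the lost values is imputation under missing at random. An analysis plan cannot recover data that were never collected. The earlier scores help least for a flare in weeks 2 to 4. The reading that folds levocetirizine into the regimen needs an item that the Interventions list does not contain.

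A reader might also infer that the ban forbids treating adverse events, since the article promises that "dermatologists will provide appropriate treatment for any adverse events encountered". That is a matter of wording only: the promise is explicit, and concomitant medications are recorded.

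**Conclusion.** The point holds in two parts. The withdrawal rule, read plainly, discards outcomes that could be collected at scheduled visits and leaves them to imputation under missing at random, when the reason may be treatment failure. Separately, the ban on additional treatment conflicts with the levocetirizine rescue.

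The size is unknown because the article gives no frequency. Per affected patient it is at most about 1.9 points (MSS) or 2.3 points (control) on the arm's EASI50 rate, if imputation returns the planning rate; under the assumed withdrawal shares above, the difference shifts by between −12.5 and +3.9 points.

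Four stronger inferences are not supported:
- That the rule contradicts intention to treat. Withdrawn patients stay in the analysis through imputation; the analysis is weakened, not contradicted.
- That the lost outcomes are necessarily related to prognosis, or always include week 4. Neither follows from the text.
- That the trial is biased in favour of MSS. The direction depends on how withdrawals split between the arms.
- That counting rescue as non-response is the only correct primary rule. That is a choice of estimand.

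An amendment should be made because the rule and the conflict are explicit and the remedy is cheap.

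**What to change.** In Interventions:
- Replace withdrawal of participation with discontinuation of study product where needed, and keep consenting patients on all Table 1 visits to week 16.
- State that levocetirizine rescue is permitted, is recorded as concomitant medication, and does not count as an emergency intervention.
- For clarity, say that treatment of adverse events is allowed and recorded in the same way.

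In Statistical analysis:
- Add at least a sensitivity analysis that counts patients with an emergency AD intervention before the week-4 assessment as EASI50 non-responders. The sponsor may make this the primary rule, with observed week-4 EASI as the sensitivity analysis.
- Keep multiple imputation for values missing for other reasons.

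Cost: a short amendment reported to the ethics committee, with no new visits. Recruitment began in August 2025, so it should be made soon and while the statisticians are blinded; outcomes of patients withdrawn before then may be lost. The downside is that some data will be collected off product or after rescue treatment, so their interpretation needs the non-responder analysis alongside.
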